#### Secondary outcome 1: mean hospital length of stay at 12-month follow-up

The mean hospital length of stay for relevant wards over the 1 month period preceding random group allocation, and the same corresponding month 12 months later. Hospital length of stay is a key driver of hospital efficiency [49–52] and provides a measure of benefit or non-inferiority for weekend allied health provision [37, 38, 53].

#### Secondary outcome 2: opportunity cost to make the decision during the intervention period at 12-month follow-up in AUD$ (time to make decision, resources used, and knowledge broker time attributable to each participant in implementation strategy group 2)

Participants will record self-reported time (person-hours) taken to make the resource allocation decision, and any resources used (e.g. librarian to conduct literature search). For implementation strategy group 2, the self-reported data will be combined with time contributed by the knowledge broker to each decision-maker. The opportunity costs involved in making a decision (e.g. staff time and resources used) will be captured using interviews with allied health managers and logs of staff time recorded by research personnel. Measures of staff time will be valued using market salary rates in AUD$, with a 33% salary “on-cost” loading to account for allowances, leave, and other employee entitlements. Understanding the cost and benefits of providing research implementation strategies can assist healthcare governance agencies making implementation resource allocation decisions.

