Item 2. “Why: describe any rationale, theory, or goal of the elements essential to the intervention”	Usual practice is the model of weekend allied health resource allocation decision-making at the research location. This serves as a pragmatic reference standard for implementation research	The evidence-based policy recommendation document will communicate research findings in an accessible format to facilitate evidence informed decision making [43]. This will be achieved by embedding an understanding of the political context within design, providing quality evidence communicated through a credible messenger, and fostering active engagement and linkages between policy-makers and researchers [44].	The evidence-based policy recommendation document will be the same as that provided to implementation strategy group 1. In addition, the knowledge broker will act as an intermediary agent to facilitate the transfer and exchange of relevant information between researchers and healthcare decision-makers to promote evidence informed decision-making [48, 49]. The knowledge broker will undertake activities focused on identifying and engaging with decision-makers, facilitating collaboration, identifying and obtaining relevant information, facilitating development of analytic and interpretive skills, creating research implementation resources, project coordination, communication and information sharing, network development, evaluating change, and supporting sustainability [48].

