### Data collection

Project investigators will collect the primary outcome data by requesting an allied health activity statistics report for the relevant wards at each hospital from the weekend allied health decision-maker/s at each health service. It will be requested that this report contains the minimum variables: number of allied health service events, date of each allied health service event, as well as hospital and ward location of each allied health service event. Where these data are not available, allied health staffing levels or budgetary allocations during weekdays and weekends for the relevant wards at each hospital in the preceding month will be requested. The mean hospital length of stay for relevant wards will be collected as reported by the hospital electronic patient management systems. Previous research has shown this data collection method for hospital length of stay provides completeness of data capture when compared to other methods [49]. Allied health managers will be encouraged to record the amount of time (person-hours) taken and other resources used (e.g. librarian) to make the resource allocation decision in a log. For implementation strategy group 2, these data will be combined with knowledge broker records of the amount of time attributed to each participant during the intervention period. Project investigators will perform audio-recorded semi-structured interviews either face to face, via telephone, or videoconference as per participant preference. Qualitative data from knowledge broker conversations will be audio-recorded, and regular communication (e.g. email, phone, online forums) with the knowledge broker will be captured.

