#### Economic evaluation

The economic analysis will calculate the “incremental cost per additional cluster and ward that completely align with the policy recommendation” of implementation strategy group 1 vs control, and implementation strategy group 2 vs control. The opportunity costs involved in making a decision, captured using interviews with decision-makers and research personnel logs of staff time involved, will be valued using market salary rates with a 33% on cost loading to account for leave and other employee entitlements. This analysis will be a trial-based evaluation. The analysis will then be fed into a net-benefit analysis which will incorporate data relating to the amount of allied health events captured at the baseline and 12-month follow-up assessments and changes in hospital length of stay. These data will then be modelled into a 5-year time horizon assuming that weekend service levels at the 12-month follow-up assessment are maintained 5 years into the future. One-way sensitivity analyses will be conducted to model the effects of having different numbers of allied health managers involved with making this decision at both the cluster and ward level.

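### The economic evaluation costs the making of the decision but not the provision of the strategy, so the policy document enters with no provision cost and shared broker work has no stated rule

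*Protocol article*

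**What the plan says.** All places are in the protocol article.

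- **Cost components.** The heading of Secondary outcome 2 limits the cost to making the decision, within the intervention period, and lists "time to make decision, resources used, and knowledge broker time attributable to each participant in implementation strategy group 2". For group 2, "the self-reported data will be combined with time contributed by the knowledge broker to each decision-maker". Staff time is also to come from interviews and "logs of staff time recorded by research personnel".
- **Broker time.** Data collection repeats the unit of recording: "knowledge broker records of the amount of time attributed to each participant during the intervention period".
- **Use in the ratio.** Economic evaluation plans an incremental cost per additional cluster and ward in full alignment, for group 1 v control and group 2 v control. Staff time is priced at market rates plus a 33% loading, and the only cost input is named in these words: "The opportunity costs involved in making a decision, captured using interviews with decision-makers and research personnel logs of staff time involved, will be valued using" (the sentence then gives the rates).
- **Purpose.** Secondary outcome 2 closes by saying that knowing the costs and benefits of providing implementation strategies can help agencies decide on such resources.
- **Work behind the document.** Table 1 (Item 4) and the section on implementation strategy group 1 describe consensus drafting by the investigators and review by a stakeholder committee. The document is emailed after allocation.
- **Work of the broker.** Table 1 (Item 2) includes in the role "creating research implementation resources, project coordination, communication and information sharing, network development, evaluating change, and supporting sustainability". Table 1 (Item 8) adds a 60-minute group webinar to the 60-minute consultation and the monthly contacts.

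**The concern.** What it costs a manager to reach a decision is not what it costs a health agency to supply a policy document or a knowledge broker. The article states the second as its purpose and defines the first. As written, group 1 v control carries no provision cost for the strategy under test, and group 2 v control carries broker time but no document cost. If the document shortens managers' searching, group 1 could show a negative incremental cost without the cost of supplying the document ever being set against that saving.

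Broker time is a separate, weaker problem. It is recorded by participant, while part of the described role serves no one participant. Without a rule for such hours, two analysts could follow the text and reach different group 2 costs.

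At stake are the two cost-effectiveness ratios and the numbers passed on to the net-benefit analysis. The primary outcome is untouched.

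**Working it through.** **1. Does any listed component cover document production?**

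- Decision time and resources used are the managers' own inputs. Time spent reading and applying the document may fall here; writing it does not.
- The research personnel logs are tied, in both Secondary outcome 2 and Economic evaluation, to the cost of making a decision.
- The outcome is limited to the intervention period. Participant timeline counts the 12 months from initial provision of the strategy, so drafting and committee review come before the window.

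No component covers it.

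**2. Does it cancel?** Both planned ratios are against control, and controls receive the document only at trial completion (Table 1, Items 3 and 8). It would cancel in group 2 v group 1, but that economic comparison is not planned. Leaving out a non-negative cost lowers the numerator, so with a positive alignment gain the ratio can only move in the strategies' favour.

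**3. Denominator of the ratio.** The article gives no cost figure to reproduce. The sample size section supplies the denominator: 25 clusters per group analysed, 27 recruited, 50% v 10% fully aligned. That statement reproduces. With two-sided 5% significance (assumed, as the article states no level), a continuity-corrected comparison of two proportions at 80% power needs 25 per group. At n = 25, power is 89% by normal approximation and 83% by Fisher's exact test.

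Additional aligned clusters per strategy arm = n × (0.50 − 0.10):
- n = 25: 10.0
- n = 27: 10.8

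**4. Effect of an uncounted document cost D.** D is an assumption throughout.
- Charged to one arm: D / 10.0 or D / 10.8.
- Shared by both strategy arms (2 × 27 = 54 clusters): D / (54 × 0.40) = D / 21.6.

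| D (AUD) | One arm, n = 25 | One arm, n = 27 | Shared by both |
|---|---|---|---|
| 5,000 | 500 | 463 | 231 |
| 10,000 | 1,000 | 926 | 463 |
| 50,000 | 5,000 | 4,630 | 2,315 |

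Entries are AUD per additional aligned cluster. The number of wards is not given, so the per-ward ratio cannot be sized.

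**5. Broker time.** Individual hours per cluster = 1 + 12f, where f is the length of a monthly contact in hours (not stated; 0.25 to 1 assumed, one participant per cluster). This gives 4, 7 or 13 hours for f = 0.25, 0.5 or 1. If S shared hours go uncounted, the share missed is (S/27) / (1 + 12f + S/27).

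| S (hours) | S/27 | f = 0.25 | f = 0.5 | f = 1 |
|---|---|---|---|---|
| 1 (webinar only) | 0.04 | 0.9% | 0.5% | 0.3% |
| 20 (assumed) | 0.74 | 16% | 10% | 5% |
| 160 (assumed) | 5.93 | 60% | 46% | 31% |

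The webinar hour alone does not matter. Materials, coordination and network work could, but their size is not in the article.

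**The case against.** The strongest defence is that document development is a sunk research cost: a one-off product made before the intervention period, used by both strategy arms and later given to controls. Spreading it over trial-sized arms would not represent wider roll-out, where the cost per cluster would fall. This perspective is legitimate, but the article does not adopt it, and its stated purpose points the other way.

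Three stronger readings are tempting and are not supported:

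- *The document costs nothing at all.* Only its provision is uncosted. Managers' time with it may be counted as decision time, other resources they use are also a listed component, and delivery is just an email.
- *Shared broker work is dropped.* The text does not say so. Time attributed to a participant can include an apportioned part of webinar or preparation time, and the research personnel logs might capture some of it. What is lacking is a rule, not an inclusion.
- *A negative incremental cost in group 1 would be an artefact.* Saved search time is a real saving to the manager. The trouble is only that it would be reported without the provision cost beside it.

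A journal article may also leave its cost inventory to a fuller plan. That would answer a missing detail. Here, however, the article prints a component list, limits it in time and carries it into a named ratio, and that list does not match its own purpose.

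**Conclusion.** The point holds for the document. As defined, the costing enters no provision cost for it in either planned ratio, the omission does not cancel against control, and it can only favour the strategies. For the broker it holds in a weaker form: nothing ensures that work serving no single participant is counted.

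The size is unknown. AUD 930-1,000 (one arm) or about AUD 463 (both arms) per additional aligned cluster for each AUD 10,000 left out rests on the planned alignment rates and an illustrative sum. A smaller observed gain would raise it in proportion. The 5% to 60% range for uncounted broker time rests on assumed contact lengths and 20 to 160 assumed shared hours, and applies only if those hours are not apportioned. A reader might infer that the net-benefit result is materially biased. That is not shown, because that analysis also brings in service events, length of stay and a five-year horizon.

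This is a correction to a secondary economic analysis. Design, sample size and primary comparison are unaffected.

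**What to change.** In Secondary outcome 2, Data collection and Economic evaluation:

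1. Add a provision-cost component, separate from the opportunity cost of making the decision, which stays as it is.
2. Make a one-off estimate of the time spent drafting, reviewing and distributing the document, valued at the same salary rates and 33% loading.
3. Report the cost per additional aligned cluster and ward twice: with document production, and without it as a sunk cost. State how the document cost is divided between the two strategy arms.
4. Have the broker's 12-month diary, already kept for adherence (Table 1, Item 11), record all time on the role. Divide hours not tied to one participant equally over the group 2 clusters, entering the webinar hour once and not once per attendee.

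The cost is a somewhat fuller diary, one estimate of document hours and one extra scenario. The ratio that includes production will look less favourable to the strategies. The diary change should be made before follow-up starts, because shared hours are hard to reconstruct afterwards.

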#### Process measures

Semi-structured interviews performed by a researcher who has not been involved in delivering the intervention at 12-month follow-up will be used to explore participant experiences concerning: (1) perceptions of the trustworthiness and sufficiency of evidence of the evidence base to guide clinical practice in this area of allied health service delivery, (2) the sources of information relied upon by allied health managers when deciding upon the model of weekend allied health service delivery they used in acute and sub-acute hospital wards and why they chose to use those sources, (3) perceived most influential source of information encountered by allied health managers when deciding upon the model of weekend allied health service delivery they used in acute and sub-acute hospital wards and why they thought this source was the most influential, and (4) perceived potential improvements to the intervention received and how it was provided. This information will be used to inform future allied health research implementation strategies.

#### Qualitative measure: perceived risks, barriers, and facilitators to adopting evidence-based policy recommendations at 12-month follow-up (implementation strategy groups 1 and 2) and during knowledge broker interactions (implementation strategy group 2 only)

Semi-structured interviews will explore what participants perceived as being the risks, barriers, and facilitators encountered in adopting or not adopting the policy recommendation. Control group participants will not be invited to participate in this final qualitative interview.

### Participant timeline

The Consolidated Standard of Reporting Trials (CONSORT) study flow diagram is provided in Fig. 1 [54]. Baseline data collection and implementation strategy group allocation are planned to occur following the participant information and consent process. A 12-month period will then be provided between initial implementation strategy provision and follow-up to allow sufficient time, on pragmatic grounds, to initiate changes required to align weekend allied health resource allocation with the evidence-based policy recommendation. Follow-up data will then be collected after the 12-month intervention period upon trial completion. The Standard Protocol Items: Recommendations for Interventional Trials (SPIRIT) flow diagram schedule of enrolment, interventions, and assessment procedures is described in Table 2 [55].

**Fig. 1 Fig1:**
[figure not shown]
CONSORT study flow diagram

**Table 2 Tab2:**
[figure not shown]
SPIRIT flow diagram: schedule of enrolment, interventions, and assessment procedures

### Sample size

The sample size estimate was calculated based on the units of assessment of the primary outcome ‘alignment of weekend allied health service provision with policy recommendations at 12-month follow-up’. The most conservative unit of assessment for this outcome will be clustered at individual hospitals/health services with geographically distinct decision makers. We therefore conducted our power analysis at this “cluster-level” rather than at the ward-level or individual decision-maker level (as one hospital/health service may have multiple decision makers involved). A sample size of 25 clusters (hospitals/health services) per group will provide greater than 80% power under the assumption that 50% of participants in an intervention group and 10% in the control group will completely align with the policy recommendation. We will aim to recruit 27 clusters (hospitals/health services) per group to allow for approximately 5–10% loss to follow-up in each group. Assumptions regarding statistical power and expected loss to follow-up were derived from a similar randomised controlled trial by Dobbins et al. [33]. Based on data from a survey of physiotherapy services provided outside business hours in Australian hospitals by Shaw et al. [41], and allied health staffing levels for health service inpatients in Victoria [56], it is anticipated that none of the recruited health services will be completely aligned with the evidence-based policy recommendation at baseline. This analysis was performed using Stata 13 (StataCorp, 2013. Stata Statistical Software: Release 13. College Station; TX: StataCorp LP).

### Recruitment

Project investigators will identify potentially eligible hospitals/health services using pre-existing professional networks and publicly available resources (e.g. government websites). Members of the research team will contact the allied health management either face-to-face, via telephone, or email and provide information regarding the study. The allied health management will then be asked if they support the research being conducted at their organisation. If support is provided, the potential participant/s responsible for weekend allied health resource allocation decisions at the health service will be identified via the allied health management. Potential participants (weekend allied health resource allocation decision-makers) will be contacted, provided with information on the study, and written informed consent will be sought for participation.

### Assignment and concealment of implementation strategy group allocation

Study investigators will consult with health service representatives to determine decision-making structure for weekend allied health services within their health network. Some health services in Australia are comprised of multiple geographically separated hospitals that report to the same board but have independent decision-making processes in relation to weekend allied health service provision decisions. They will be treated as separate units of recruitment and randomisation, where health service representatives report that decision-making for geographically distinct hospitals is independent and that they anticipate ability to prevent contamination of the intervention between sites within their network. Units of randomisation (hospitals or health services) will then be stratified according to geographic location. A random number sequence will be generated using an online software application (Sealed Envelope Ltd. 2018. Create a blocked randomisation list. [Online] Available from: https://www.sealedenvelope.com/simple-randomiser/v1/lists), incorporating permuted blocks of randomly selected sizes of three, six, or nine, and stratified according to metropolitan or regional status. This random number sequence will be generated and held by a single investigator ([name]) in a secure location so that investigators conducting recruitment and data collection are blinded to the allocation status of participating sites and the allocation of the next site to be recruited.

### Blinding

Participant weekend allied health decision-makers will not be blinded to group allocation. It will be clear to participants which implementation strategy group they have been allocated due to the nature of the trial, thus it is not possible to blind participants. In order to maintain allocation concealment, site allocation to implementation strategy group 2 will only be revealed to the knowledge broker once the site has been recruited and baseline data collected. Investigators performing data collection will be blinded to participant implementation strategy group allocation for the duration of the study. Investigators performing qualitative interviews will not be blinded. The trial data analyst will be blinded to group allocation. Three mock codes representing different sequence allocation will be used to blind the statistician conducting the final quantitative data analysis from the identity of each hospital/health service and the implementation strategy group allocation.

### Data collection

Project investigators will collect the primary outcome data by requesting an allied health activity statistics report for the relevant wards at each hospital from the weekend allied health decision-maker/s at each health service. It will be requested that this report contains the minimum variables: number of allied health service events, date of each allied health service event, as well as hospital and ward location of each allied health service event. Where these data are not available, allied health staffing levels or budgetary allocations during weekdays and weekends for the relevant wards at each hospital in the preceding month will be requested. The mean hospital length of stay for relevant wards will be collected as reported by the hospital electronic patient management systems. Previous research has shown this data collection method for hospital length of stay provides completeness of data capture when compared to other methods [49]. Allied health managers will be encouraged to record the amount of time (person-hours) taken and other resources used (e.g. librarian) to make the resource allocation decision in a log. For implementation strategy group 2, these data will be combined with knowledge broker records of the amount of time attributed to each participant during the intervention period. Project investigators will perform audio-recorded semi-structured interviews either face to face, via telephone, or videoconference as per participant preference. Qualitative data from knowledge broker conversations will be audio-recorded, and regular communication (e.g. email, phone, online forums) with the knowledge broker will be captured.

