### Eligibility criteria

Allied health managers responsible for weekend allied health resource allocation decisions will be eligible for inclusion. All allied health professions currently providing an inpatient service to acute general medical and surgical wards, and sub-acute rehabilitation wards are eligible. A representation of the different allied health professions (e.g. physiotherapy, occupational therapy, speech pathology, dietetics, podiatry, psychology, exercise physiology, and social work) will be sought. We shall include those who currently provide weekend allied health services as well as those who do not currently provide services, but could potentially introduce these services.

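### The primary outcome report is requested from the unblinded manager whose decision it judges, with no independent check stated and no ward list stated to be fixed before allocation

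*Protocol article*

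**What the plan says.** **Who is studied and what they know.** Under Eligibility criteria, "Allied health managers responsible for weekend allied health resource allocation decisions will be eligible for inclusion". Under Blinding, "Participant weekend allied health decision-makers will not be blinded to group allocation".

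**Who supplies the outcome.** Under Data collection, the stated procedure for the primary outcome is "requesting an allied health activity statistics report for the relevant wards at each hospital from the weekend allied health decision-maker/s at each health service". The least that the report should hold is "number of allied health service events, date of each allied health service event, as well as hospital and ward location of each allied health service". If events are unavailable, staffing levels or budget allocations are requested instead. No other source is named for these, and no verification is described.

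**Who is blinded.** "Investigators performing data collection will be blinded to participant implementation strategy group allocation for the duration of the study", and "The trial data analyst will be blinded to group allocation".

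**What each group holds.** The Interventions section says the document sent to group 1 contains specific recommendations on the share of services to be delivered at weekends. Group 2 receives the same document. Controls receive it at trial completion.

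**What is measured.** Under the primary outcome, the weekend share of service events on the relevant wards over one month determines whether a cluster is fully, partially or not aligned. Acute and sub-acute wards are considered separately. Baseline and follow-up use the same calendar month.

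**The concern.** Blinding a data collector protects an outcome when the collector makes the measurement. Here the collector receives a report supplied by the person whose allocation decision is being assessed. That person knows the group and, in two groups of three, has been given the recommendation against which the report will be scored. Blinding further down the line cannot undo anything that happened before the report arrived.

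The room for judgement lies mainly in scope. The eligible ward types are stated (acute general medical and surgical, and sub-acute rehabilitation), but the article does not say who lists the individual wards, who labels a mixed ward, or whether the list is settled before allocation and carried to 12 months. Because full alignment requires both ward types to be aligned, ward scope and labels could affect the category. The Analysis section also plans the primary analysis at ward level, where scope decides which units are analysed.

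At stake is whether a difference between groups reflects changed service provision or partly reflects how it was reported.

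**Working it through.** **1. The chain of information**

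| Step | Who | Knows the group? | Given the recommended proportions? |
|---|---|---|---|
| Makes the allocation decision | Participant manager | Yes | Groups 1 and 2 only |
| Is asked for the 12-month report or fallback data | Same manager | Yes | Groups 1 and 2 only |
| Receives the report | Investigator | No | Not relevant |
| Analyses | Statistician | No | Not relevant |

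The protocol blinds the last two rows. The exposure is in the second, and it differs by group.

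**2. The plan's own figure**

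Inputs from Sample size: 25 clusters per group, with 50% against 10% completely aligned. No significance level is stated there, so I assume two-sided 0.05. With a pooled rate of 0.30:

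power = Φ[(0.40·√25 − 1.96·√(2·0.30·0.70)) / √(0.50·0.50 + 0.10·0.90)]
= Φ[(2.000 − 1.270) / 0.583] = Φ(1.25) = 89.5%

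Exact enumeration gives 83.3% for Fisher's test and 91.1% for the uncorrected chi-square test. The stated power above 80% reproduces, and this point does not affect it.

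**3. Weight of one cluster**

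1/25 = 4 percentage points of a group's rate. The planned difference is 40 points, so one misclassified cluster is 4/40 = one tenth of it.

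**4. What misclassification would do: illustration only**

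The misreporting rates here are assumed and appear nowhere in the document. Suppose true full alignment is 10% in both groups, and a share m of the non-aligned intervention clusters is reported as aligned. The apparent intervention rate is 0.10 + 0.90m, and the expected number of misreported clusters is 25 × 0.90 × m = 22.5m. The last two columns give the chance of a false significant result favouring the intervention, with 25 clusters per group.

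| m | Apparent rate | Clusters affected | Chi-square | Fisher |
|---|---|---|---|---|
| 0 | 10.0% | 0 | 2.4% | 0.4% |
| 5% | 14.5% | 1.1 | 7.2% | 2.4% |
| 10% | 19.0% | 2.25 | 15.0% | 7.1% |
| 20% | 28.0% | 4.5 | 38.9% | 25.2% |

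These are tests on full alignment as a yes/no outcome, the basis of the sample size. The planned analysis is a signed-rank test on three ordered categories, so the table shows sensitivity and does not predict the trial's error rate.

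**The case against.** The strongest defence is that this is a request for records, not a self-rating. The report must list each event with its date, hospital and ward, and events follow a nationally endorsed data set definition. A comparable report exists from baseline for the same calendar month, so a blinded investigator could notice a ward that appears or disappears. The article is also condensed, and site ward lists are operational detail that a fuller protocol may hold. Much of this stands. It limits what could be distorted, and it means that silence about the ward list is not proof that the list is open. It does not remove the point: no rule is stated for a ward that changes between reports, no check against a source is stated, and the fallback data lack the event-level detail.

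Four stronger readings are tempting but not supported:

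- **The manager produces the report or chooses the wards.** The text says only that the report is requested from the manager. It does not say who compiles it or selects the wards.
- **The knowledge broker may help with the outcome figures, so bias is greatest in group 2.** Table 1 lists "network development, evaluating change, and supporting sustainability" among the broker's activities, but as general role items. The concrete tasks are a needs assessment, a 12-month plan, one webinar and monthly contact. None involves outcome data.
- **Length of stay already follows a manager-independent route.** The text says "The mean hospital length of stay for relevant wards will be collected as reported by the hospital electronic patient management systems", which names a system but not who requests or extracts the data.
- **A bias of some stated number of points is to be expected.** Any such figure depends on an assumed number of affected clusters.

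**Conclusion.** The point holds as a risk of bias, not as demonstrated bias. An unblinded participant supplies the data that judge the participant's own decision. Only the intervention groups are given the recommended proportions during the trial. The stated blinding acts after the report has been supplied.

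The likely direction favours both intervention groups over control. That rests on the assumption that knowing the recommendation can influence what is supplied, and the document offers no evidence for or against it. The size cannot be derived: it is 4 points per misclassified cluster, with an unknown number of clusters. The event-level content and the baseline report make large distortion less likely where events are available. They offer less protection where staffing or budget figures are used. The sample size is unaffected. The change is worth making because it is cheap and concerns the primary outcome, and because differential reporting could not be repaired at analysis.

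**What to change.** 1. Before allocation, record for each cluster the included wards, the acute or sub-acute label of each, and the data source (events, staffing or budget), taken from the baseline report. Use the same list, labels and source at 12 months. Documented ward closures or openings are the only exceptions.
2. Where a hospital information system or data custodian holds the event data, request the date-stamped extract there at both time points. The manager only authorises the request.
3. Have the blinded investigator compute the weekend proportion and assign the alignment category from the extract.

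**Cost:** one baseline form per cluster and a different addressee for the data request. The downside is that some hospitals may hold event data only within the allied health department. There the manager-supplied report is kept, with the locked ward list, so the risk is reduced at those sites but not removed.
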